**Discussion:**

Potential implications of this trial are multifaceted: should the primary outcome be fulfilled and the treatment be safe, one may envisage that IFNβ-1a be used to reduce the infectivity of patients with mild-to moderate disease. In case IFNβ-1a reduced the duration of hospital stay and/or ameliorated the clinical status, it may become a cornerstone of COVID-19 treatment.

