#### Secondary outcomes

I)Improvement in clinical severity score, defined as percentage of patients reporting each severity rating on a 7-point ordinal scale (as defined above in the “Eligibility criteria {10}” section). [Time frame: baseline, days 7, 15, 21, and 29]. This study is underpowered to measure clinical efficacy. Nevertheless, measuring changes in the distribution of patients on the 7-point ordinal scale allows both to monitor the safety of the therapeutic regimen and detect potential positive changes in the clinical status of patients.Improvement in clinical severity score, defined as the time to clinical improvement of two points from the time of randomization on a 7-category ordinal scale or live discharge from the hospital, whichever comes first (as defined above in the “Eligibility criteria {10}” section). [Time frame: from baseline to day 29].Incidence of new oxygen use, non-invasive ventilation, or high flow oxygen devices during the trial. [Time frame: from baseline to day 29].Oxygenation free days in the first 28 days. [Time Frame: from baseline to day 29].Ventilator free days in the first 28 days. [Time frame: from baseline to day 29].Incidence of new mechanical ventilation use during the trial. [Time frame: from baseline to day 29].Number of patients transferred to Intensive Care Unit (ICU). [Time frame: from baseline to day 29].II) Mortality rate. [Time frame: from baseline to day 29].III) Changes from baseline in pulmonary CT imaging severity score measured with artificial intelligence and expressed as cc and percent values of diseased lung (lung consolidation, ground glass opacities and disease free) [Time frame: baseline, day 21; extra follow-up at 90 days].IV) Duration of hospital stay expressed in days. [Time frame: from baseline to day 29].V) Viral load measured on plasma with RT-PCR. [Time frame: baseline, days 3, 5, 7, 9, 11, 13, 15, 21, and 29].VI)Number of serious adverse events (SAE) and adverse drug reaction (expected and un-expected) until the discharge from the clinical unit (discharge for any motivation). [Time frame: from baseline to day 29]. This outcome addresses safety.Changes from baseline in white blood cell count (WBC), hemoglobin, platelets, C-reactive protein (CRP), lactate dehydrogenase (LDH), alanine aminotransferase (ALT), aspartate aminotransferase (AST), total bilirubin, creatinine, prothrombin time, international normalized ratio (INR), D-dimer, electrolytes (sodium, potassium, calcium), and glucose. [Time frame: baseline, days 7, 15, and 29]. IFNβ exerts broad-range effects on the immune system, being anemia, thrombocytopenia, and leukopenia reported as common events [21]. Thus, monitoring these markers, in conjunction with markers of inflammation, coagulation, and organ dysfunction, is of pivotal relevance to address safety.

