### Statistical methods

#### Statistical methods for primary and secondary outcomes {20a}

Prior to the analysis of the final study data, a detailed statistical analysis plan (SAP) will be written describing all analyses that will be performed. Continuous variables will be described by mean, standard deviation, median, minimum, and maximum. Categorical variables will be described by number and percentage of subjects in each category. The primary efficacy analysis will be done on an intent to treat basis (ITT) and will include all randomized patients. Survival analysis will be performed to address the primary outcome of the study. Time to event is defined as the time from randomization until date of negative conversion. The date of the event (time of negative conversion) is the date of the first negative nasal swab test, confirmed by a second test performed at least 48 h apart. Data for dead patients are censored at the time of the last nasal swab. Survival curves will be estimated using the Kaplan-Meier method and the Log-rank test will be used to compare the outcomes of the different treatment arms. Hazard ratios will be estimated using the Cox proportional hazards model and these will be presented together with 95% two-sided confidence intervals. Endpoints that are measured as time from randomization will be compared between treatment groups using the Log-rank test. Student’s *t* test or Mann-Whitney test (depending on the data distribution pattern) will be used for inter-group comparison of continuous variables; chi-square test or Fisher exact test will be used for inter-group comparison of categorical variables. The primary analysis set for safety analyses is defined as the safety analysis set, which will include all participants who are randomized and have received at least 1 dose of study treatment. All safety data collected from the randomization date through the last follow-up visit will be summarized by treatment group. Statistical significance will be determined at 5% significance level. Analysis will be performed by SAS software Version 9.2 or later (SAS Institute, Inc., Cary, North Carolina, USA).

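### Hospital stay in days has no rule for deaths, so in-hospital deaths can count as short stays; time to live discharge would avoid this

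*Protocol article*

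**What the plan says.** In the protocol article, Outcomes {12}, secondary outcome IV reads "IV) Duration of hospital stay expressed in days. [Time frame: from baseline to day 29". It does not say what value a patient who dies in hospital receives.

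Statistical methods {20a} offers two rules that could apply. For continuous measures, the t test or "Mann-Whitney test (depending on the data distribution pattern) will be used for inter-group comparison of continuous variables". For times, "Endpoints that are measured as time from randomization will be compared between treatment groups using the Log-rank test". Hospital stay is not assigned to either. The only rule for deaths in that section is "Data for dead patients are censored at the time of the last nasal swab", which is tied to swabs and so fits the primary endpoint alone. Section {20c} adds that missing data are not replaced and that analysis uses observed cases.

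The Discussion part of the abstract says that in case IFNβ-1a "reduced the duration of hospital stay and/or ameliorated the clinical status, it may become a cornerstone of COVID-19 treatment".

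Elsewhere in the secondary outcomes, the second item of outcome I counts only live discharge, whereas outcome VI follows adverse events until discharge for any reason. Outcome IV specifies neither. Outcome I also lists "Oxygenation free days in the first 28 days" and "Ventilator free days in the first 28 days", again with no score for deaths.

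**The concern.** A shorter stay is good only if the patient leaves alive. If the day of death is taken as the end of the stay, an early death enters the comparison as a favourable value. The arm with more early deaths then gains on this outcome.

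Deaths have to be expected. Eligibility {10} admits patients in category 5 (high-flow oxygen or non-invasive ventilation), and mortality is itself a secondary outcome. What is at stake is the reading of a secondary outcome that the abstract puts forward, joined by and/or with clinical status, as a possible reason for wider use of the drug.

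**Working it through.** **Plan's own figure.** None exists on this point: the article gives no expected length of stay and no expected mortality. The arm sizes used below (84 and 42) come from Sample size {14}, which concerns the primary endpoint only.

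**Step 1: each reading of the text.**

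- *t test or Mann-Whitney, death ends the stay.* This is the natural reading of a number of days. A death on day 5 ranks ahead of a live discharge on day 12.
- *Log-rank, death counted as end of stay.* Same bias: death and discharge are the same event.
- *Log-rank, deaths censored at death.* Censoring is informative. The dead are treated as if they kept the survivors' later chance of discharge, so the Kaplan-Meier curve overstates discharge.
- *Deaths dropped as not observed.* The comparison is confined to survivors and loses the protection of randomization.

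None of these counts an in-hospital death as a failure to be discharged.

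**Step 2: direction by simple arithmetic (assumed inputs).** Let survivors stay L days on average in both arms, let deaths occur at day D on average, and let mortality be p. Mean stay is (1 − p) × L + p × D. With L = 14 and D = 8:

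- IFNβ-1a, p = 15%: 0.85 × 14 + 0.15 × 8 = 13.1 days
- control, p = 5%: 0.95 × 14 + 0.05 × 8 = 13.7 days
- difference: (0.15 − 0.05) × (8 − 14) = −0.6 day, in favour of the arm with three times the deaths.

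Scoring deaths at 29 days instead gives (0.15 − 0.05) × (29 − 14) = +1.5 days. The sign depends on the unstated rule. It also depends on D being smaller than L: with deaths at day 20 on average, the first rule gives 0.10 × (20 − 14) = +0.6 day.

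**Step 3: effect on the test (simulation, assumed inputs).** 84 versus 42 patients; live-discharge times identical in both arms (lognormal, median 12 days, sigma 0.6, capped at day 29); death times exponential with median 7 days, capped at day 28; two-sided Mann-Whitney at 5%; 4,000 runs per row. Differences are IFNβ-1a minus control. False benefit means a significant result with the shorter mean stay on IFNβ-1a.

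| Mortality, IFNβ-1a vs control | Difference, death ends stay | False benefit | Difference, deaths scored 29 | False benefit |
|---|---|---|---|---|
| 5% vs 5% | 0.0 day | 2.6% | 0.0 day | 2.4% |
| 10% vs 5% | −0.2 | 3.8% | +0.7 | 0.9% |
| 15% vs 5% | −0.4 | 5.0% | +1.5 | 0.1% |
| 20% vs 5% | −0.6 | 6.9% | +2.2 | under 0.1% |
| 20% vs 10% | −0.4 | 4.8% | +1.5 | 0.2% |
| 30% vs 10% | −0.8 | 9.5% | +3.0 | under 0.1% |

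The simulation standard error is about √(0.026 × 0.974 / 4000) = 0.25 percentage points at 2.6%, and about √(0.095 × 0.905 / 4000) = 0.46 at 9.5%.

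**The case against.** The strongest reply is that the article assigns no test to hospital stay, never says that death ends the stay, and announces a detailed SAP that could settle both. An article need not spell out the scoring of a secondary outcome. This stands against any claim that the plan prescribes a wrong analysis. It does not remove the point, because the outcome is defined here, in days, and Step 1 shows that neither test the article offers handles deaths properly without a further rule.

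Three stronger readings are tempting, and the documents do not support them.

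- A reader might infer that the plan states that hospital stay is compared as a plain continuous variable. That is the natural reading, but the log-rank rule could also apply.
- A reader might infer that the free-day counts carry the same bias. They do so only if days after death are counted as free. If only days alive and off support count, an unventilated death at day 5 scores about 5, against 28 for a never-ventilated survivor, so death is penalised. The text is silent, and an SAP can fill that gap.
- A reader might infer that a shorter stay would by itself establish the drug. The abstract says only that it may become a cornerstone. It sets no decision rule and does not name free days, and the article concedes that the study is underpowered for clinical efficacy.

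It is also fair to say that excess deaths would not be hidden. Mortality is a separate secondary outcome, and death is category 7 on the ordinal scale. That limits the harm but does not make the hospital-stay comparison valid.

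Lastly, time to live discharge overlaps with the second item of outcome I. For patients entering in category 3 or 4, a two-point improvement already means leaving hospital, so the two differ only for category 5 entrants. This is a real cost in redundancy.

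**Conclusion.** The point holds for hospital stay. As defined, outcome IV lets in-hospital deaths enter as short stays on the natural reading, and the log-rank alternative either repeats the bias or replaces it with informative censoring. When deaths come earlier than the typical discharge, an excess of deaths on IFNβ-1a shifts the comparison towards apparent benefit.

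The size is modest: 0.2 to 0.8 day across the mortality differences assumed, with the chance of a significant false benefit between 3.8% and 9.5% against 2.6% at equal mortality. These figures rest on assumed mortality, stay and death-time distributions, none of which is in the documents, and on the reading that death ends the stay. The effect under censoring at death was not quantified.

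This is a cheap improvement to a secondary outcome and leaves the primary analysis untouched. For the oxygen- and ventilator-free days, only a clarification is needed.

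**What to change.** Analyse outcome IV as time from randomization to live discharge, up to day 29, in line with outcome I. Keep patients who die in the risk set as not discharged through day 29, and censor those still in hospital at day 29. Show cumulative incidence of live discharge by arm and compare with Gray's test, or with a log-rank test in which deaths are carried to day 29. Without dropout before day 29, the two tests agree.

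Separately, state in one sentence how a death by day 28 is scored in the oxygen-free and ventilator-free day counts.

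The cost is wording and standard code. Discharge and death dates are already needed for outcomes I, II and IV. The downside is that the comparison becomes one of discharge rates and not of mean days; days of stay can still be reported descriptively, by vital status.

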#### Adverse event reporting and harms {22}

All adverse events (AEs) and adverse drug reactions (ADRs) regardless of seriousness or relationship to Medicinal Product or expectedness will be recorded daily on the corresponding page(s) included in the case report form (CRF). Whenever possible, symptoms will be grouped as a single syndrome or diagnosis. The investigator will specify the date of onset, maximal intensity, action taken with respect to the Medicinal Product, corrective therapy given, outcome, and his/her opinion as to whether there is a reasonable possibility that the event was caused by the study Medicinal Product.

Reports of serious AE (SAE) or serious ADRs, i.e., those events or reactions that result in death, life-threatening conditions, or prolongation of hospitalization, will be provided to the competent Authorities if requested.

The investigator will report all SAE immediately to the promoter and ethics committee. The investigator must fill the SAE report no later than 15 days. For reported deaths of a subject, the investigator shall supply the promoter and ethics committee with any additional information requested.

Once a year throughout the trial, the investigator will provide to competent regulatory authorities and the ethics committee an annual safety report, that is a list of all suspected serious ADRs which have occurred over this period and a report of the subjects’ safety.

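### Secondary outcome VI stops counting SAEs and adverse reactions at discharge, which conflicts with its own day-29 time frame and with the safety window in the statistical methods

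*Protocol article*

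**What the plan says.** The protocol article describes the safety window in three sections.

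- **Secondary outcomes, item VI.** SAEs and ADRs are counted "until the discharge from the clinical unit (discharge for any motivation"). The same item then states "Time frame: from baseline to day 29]. This outcome addresses safety".
- **Statistical methods {20a}.** "All safety data collected from the randomization date through the last follow-up visit will be summarized by treatment group". No stop at discharge is mentioned and no exposure-adjusted safety analysis is stated. The tests named for group comparisons are chi-square or Fisher for categorical variables and t or Mann-Whitney for continuous ones.
- **Adverse event reporting and harms {22}.** All adverse events and reactions "will be recorded daily on the corresponding page(s) included in the case report form (CRF"). No end date is given.

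Two other statements bear on the point. Secondary outcome IV is "Duration of hospital stay expressed in days", so time in hospital is itself compared between arms. The Discussion part of the abstract raises a shorter stay as a possible benefit: "In case IFNβ-1a reduced the duration of hospital stay and/or ameliorated the clinical status". The intervention section plans dosing over 2 weeks.

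**The concern.** One safety count has been given different end points, and the choice between them matters. Discharge happens after randomisation and may depend on treatment. A count that ends at discharge gives each patient an observation time set by that patient's own course. If the treated arm leaves sooner, it has fewer days in which an event can be counted, and it looks safer at the same true event rate.

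The discharge stop also falls badly against the dosing period. A patient who leaves before two weeks drops out of the safety count while still within the planned treatment period. The words about any reason for discharge may also be read to cover transfer to another unit, in which case counting would end there too.

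**Working it through.** **Step 1. Compare the stated windows.**

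| Place | Start | End |
|---|---|---|
| Outcome VI, text | not stated | discharge from the unit, any reason |
| Outcome VI, time frame | baseline | day 29 |
| Statistical methods {20a} | randomisation | last follow-up visit |
| Adverse event reporting {22} | not stated | not stated (daily recording) |

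The two parts of outcome VI can be reconciled only by reading them as discharge or day 29, whichever comes first. That reading still conflicts with {20a} and keeps the discharge stop.

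**Step 2. What the discharge stop would do, if followed.** The protocol gives neither length of stay nor SAE rates, so it has no figure of its own to reproduce here. All inputs below except the 29 days are assumptions:

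- SAE hazard h = 0.01 per day, constant, equal in both arms, and the same before and after discharge.
- Exponential time to discharge with median m, so l = ln 2 / m.
- Medians of 7, 8, 10, 12 and 14 days. The pair 7 and 12 has the same values as the swab-conversion medians in the sample size section. They are not length-of-stay data.

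Risk of a first counted event before discharge or day 29:

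R(m) = h/(h + l) × [1 − exp(−(h + l) × 29)]

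For m = 7: l = 0.0990, h + l = 0.1090, R = 0.0917 × (1 − 0.0424) = 0.088.
For m = 12: l = 0.0578, h + l = 0.0678, R = 0.1476 × (1 − 0.1401) = 0.127.

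Fixed window: 1 − exp(−0.01 × 29) = 0.252 in both arms.

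| Median stay (days) | Counted risk | Share of day-29 risk not counted |
|---|---|---|
| 7 | 0.088 | 1 − 0.088/0.252 = 65% |
| 8 | 0.097 | 61% |
| 10 | 0.113 | 55% |
| 12 | 0.127 | 49.6% |
| 14 | 0.138 | 45% |

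Risk ratios, IFNβ-1a to control, with no true difference:

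- 7 vs 12 days: 0.088/0.127 = 0.69
- 8 vs 12 days: 0.097/0.127 = 0.77
- 10 vs 14 days: 0.113/0.138 = 0.82
- equal stays, or a fixed 29-day window: 1.00

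**Step 3. Sensitivity to the hazard.** Halving or doubling h in the same formula hardly moves the ratio. For 7 vs 12 days, h = 0.005 gives 0.0457/0.0668 = 0.68 and h = 0.02 gives 0.1627/0.2302 = 0.71. A hazard that falls after discharge would reduce the share lost. In the limit of no events after discharge, nothing is lost and the two windows give the same count.

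**Step 4. Cross-check on observation time.** Mean observed days = (1 − exp(−29 l))/l. This gives 9.5 days for a 7-day median and 14.1 for a 12-day median (ratio 0.68), and 12.5 vs 14.1 for medians of 10 vs 12 (ratio 0.89). With equal 12-day medians the ratio is 1.00, but about half of the 29 days is still unobserved (1 − 14.1/29 = 0.51).

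**The case against.** The strongest reply is that the analysis text governs. If the window in {20a} is applied, post-discharge events are included and there is no bias. Daily recording in {22} has no stated end, and discharged patients enter a follow-up programme. This stands to the extent that a reader may not infer that the trial will in fact count only to discharge. What is shown is conflicting wording, one version of which is harmful.

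A reader might also infer that unequal observation is built in. It is not. It needs IFNβ-1a to change time to discharge, which the protocol treats as a possibility. The sample size assumes an effect on swab conversion only, and the protocol calls itself underpowered for clinical efficacy.

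A reader might infer that counting stops for the sickest patients. The protocol never calls ICU transfer a discharge; that is one reading of the clause. Deaths, ICU transfers and new mechanical ventilation are separate outcomes followed to day 29 with no discharge stop, and laboratory safety markers are measured at days 7, 15 and 29. The possible gap concerns other SAEs and ADRs.

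A reader might infer that most events are always lost. At the assumed 1% per day, the loss is just under half for a 12-day median stay and 45% for 14 days. A constant hazard probably overstates it, since discharge usually marks recovery.

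Finally, {22} describes serious events as "those events or reactions that result in death, life-threatening conditions, or prolongation of hospitalization", without new hospitalisation. That concerns how events are classified, not how long patients are observed, and it does not strengthen this point.

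**Conclusion.** The conflict between outcome VI and {20a} is established from the text. The consequence is conditional on two things: that the discharge wording is the one followed, and that treatment changes time to discharge. Under both conditions, and with the assumed equal and constant hazard and exponential stays, a crude risk ratio of about 0.69 to 0.82 would appear with no true difference in safety. Under the first condition alone the ratio stays at 1.00, but events after discharge are still missed. Across the assumed medians, about 45% to 65% of day-29 events would be uncounted, fewer if the hazard falls after discharge. These sizes are illustrations, because the protocol gives no length-of-stay or SAE rates. The documents do not support saying that the safety comparison is biased as planned. They support saying that one of its stated windows could bias it and should be removed.

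**What to change.** In secondary outcome VI, delete "until the discharge from the clinical unit (discharge for any motivation" together with its closing bracket. Count SAEs and ADRs from randomisation to day 29 in every patient, regardless of discharge or transfer. Collect them at the assessments already scheduled to day 29 (days 15, 21 and 29 for patients who have left). State the same window in {20a}, so that outcome and analysis agree. Planned observation time is then equal between arms, apart from deaths and dropouts.

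The cost is a wording change and slightly more case report form work after discharge. No new visits are needed.

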
#### Exploratory outcomes

I)Cytokine and inflammatory profile changes from baseline (IL-6, ferritin, procalcitonin). [Time frame: baseline, days 7, 15, and 29]. Monitoring changes in markers of inflammation may help elucidate the complex and pleiotropic effects of IFN β-1a in vivo*.*White blood cell count (WBC), hemoglobin, platelets, CRP, LDH, prothrombin time, INR, D-dimer, glucose changes from baseline. [Time frame: baseline, days 7, 15, and 29]. In addition to addressing safety, these markers may help understand the effects of IFNβ-1a in vivo*.*II) Plasma and peripheral blood mononuclear cell mRNA expression profile of interferon-stimulated genes (ISG). Analysis of differentially expressed genes between the two groups. [Time frame: baseline, day 15]. This outcome may address whether route of administration and dose are adequate to obtain an effective immune response.III) Antibodies to SARS-CoV-2 measured by a newly developed luciferase immunoprecipitation system (LIPS) assay, measuring IgA, IgM, and IgG against RBD (receptor-binding domain RBD) and S (spike) proteins [Time frame: baseline, days 7, 15, and 29].IV) Antibodies to IFNβ-1a measured by a LIPS modification of a previously developed assay [22] [Time frame: baseline, days 7, 15, and 29]. A humoral response to IFNβ-1a is common among chronically treated patients with multiple sclerosis and may result in therapeutic resistance [23]. Whether a similar mechanism takes place in patients with COVID-19 treated with IFNβ-1a needs to be ascertained.

